#### Communication with participants

Email will be the primary channel to communicate with participants for information and reminders about:

1. start of the trial (followed up with 2 fortnightly reminders)

2. instructions for installing and using prescribing data extraction tool

3. post-trial survey

4. education points notification and summary of main results

#### Subject withdrawal

Participants who formally withdraw from the study are contacted by telephone to determine reason for withdrawal. Similarly participants who do not use QC nor provide prescribing data are contacted to determine reasons for not completing the study.

### Sample size considerations

Sampling unit is the GP and the unit of analysis is also the GP. We provide the following example to demonstrate that the RCT sample size will be more than sufficient for detecting statistically significant prescription changes in medication areas where there is a shift in evidence. The example used to verify the design is measuring a 10% increase in use of preventer medications (glucocorticoid inhaled medications) in Asthma. Currently on average, 53% of GP encounters for asthma lead to the prescription of a preventer medication [13]. We expect that access to QC will promote the use of preventer medication by GPs who use the intervention. We expect that in the intervention group – at least 58.4% of GP encounters for asthma lead to the prescription of a preventer medication.

As the prescriptions belonging to the same GP will tend to be correlated, the sample size calculations estimated the average number of condition-specific prescriptions per GP and adjustments were made for intracluster correlation factor estimated to be 0.02 [14].

The number of GPs required in each arm to detect a 10% change in average prescription rate per 100 condition-specific encounters per GP are listed in Table 4[15]. Given that data collection in the trial will run for a minimum of 12 months 100 GPs in each arm will be sufficient to detect a 10% change in prescriptions (p = 0.05, power = 0.80).

### Statistical analyses

All registered participants will have completed the pre-trial survey. The subset of the intervention group analysed for primary outcome will have completed the post-trial survey and provided prescribing data. Participants in intervention group who encounter technical difficulties in using QC will be excluded from this analysis (i.e. those who had the opportunity to use QC but did not do so will be included). All of the control group except those who did not provide prescribing data will be included in the primary analysis. As summarised in Table 5 the intervention and control groups will be compared for baseline differences in prescription patterns, case-mix and profile of participants. Using an intention to treat analysis adjusted data will be analysed to determine differences in prescribing patterns and non-pharmacological management in identified priority areas, and areas in which there have been recent changes in response to new evidence using a one-tailed binomial test for proportions. Self-reported changes in diagnosis, patient education, prescriptions, investigations, referrals will also be examined. Utilisation and outcome measures will be analysed relative to QC usage and patient load (e.g. by number of patients seen).

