## Methods

### Study aims

The aim of this trial is to assess the effectiveness of an online evidence retrieval system (QC) in improving clinical decision-making processes in general practice.

The specific hypotheses to be tested in this study are that:

1. Online evidence systems are clinically acceptable and will be used by clinicians in 'real world' general practice settings.

2. Online evidence systems are effective in changing clinical decision-making behaviour and result in measurable improvements in evidence-based prescribing decisions.

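### The primary prescribing analysis is labelled intention to treat but applies two post-randomisation filters to the QC arm only, leaving the comparison open to selection bias of unknown size and direction

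*Protocol article*

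**What the plan says.** All the rules are in the Statistical analyses section of the protocol article.

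- **QC arm, data and survey:** "The subset of the intervention group analysed for primary outcome will have completed the post-trial survey and provided prescribing data".
- **QC arm, technical problems:** "Participants in intervention group who encounter technical difficulties in using QC will be excluded from this analysis". A parenthesis adds that "those who had the opportunity to use QC but did not do so will be included".
- **Control arm:** "All of the control group except those who did not provide prescribing data will be included in the primary analysis".
- **Label:** "Using an intention to treat analysis adjusted data will be analysed to determine differences in prescribing patterns".
- **Use of QC:** a separate sentence says "Utilisation and outcome measures will be analysed relative to QC usage and patient load".

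Three other sections bear on this. Data collection says that the post-trial survey goes to all participants at 12 months, and that prescribing data come electronically from both arms, covering the 12 months before the trial and the 12 months of it. Randomisation, blinding and allocation concealment says that GPs learn their allocation only after consent and the pre-trial survey, and that they cannot be blinded. Outcomes makes acceptance and use of QC a primary outcome alongside changed decision-making, in line with the first hypothesis in Study aims: "Online evidence systems are clinically acceptable and will be used by clinicians in 'real world' general practice settings".

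**The concern.** An intention-to-treat comparison keeps GPs in the analysis as randomised, whatever happens to them afterwards. Here a QC-arm GP must meet three conditions after randomisation and a control GP only one. If the GPs lost to the two extra conditions prescribe differently from those who stay, the arms differ even when QC does nothing. The protection given by randomisation is lost for the main efficacy claim, while the label tells readers that it is intact.

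Neither extra condition is needed for the prescribing outcome. The survey does not supply it, and since controls complete the same survey, even a survey requirement could have been applied to both arms. Technical difficulty with QC can occur only where QC was given, so excluding for it can never be symmetric.

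**Working it through.** **1. The conditions side by side**

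| Condition for entering the primary prescribing analysis | QC arm | Control arm |
|---|---|---|
| Prescribing data provided | required | required |
| Post-trial survey completed | required | not required |
| No technical difficulty using QC | required | cannot apply |

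The first row is symmetric and is not at issue. The second and third rows are arm-specific and are determined after allocation is known.

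**2. The plan's own figures**

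Sample size considerations gives 53% for controls, at least 58.4% for QC, an intracluster correlation of 0.02 and 100 GPs per arm. The target difference is 58.4 − 53 = 5.4 points. The 100 GPs can be neither confirmed nor refuted, because the number of asthma encounters per GP is not in the text and Table 4 is not shown. For p = 0.05 and power 0.80, without continuity correction, 100 GPs suffice from 13 encounters per GP (one-sided) or 18 (two-sided). The point made here does not depend on that figure.

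**3. How large the shift could be, on assumed inputs**

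The article gives neither the share of the QC arm that would be removed nor how those GPs differ. Both are assumptions below, and only the asthma example is used.

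- Between-GP SD implied by the plan: √(0.02 × 0.53 × 0.47) = 0.0706, or 7.1 points.
- Assume that a share q = 0.25 is removed and that retention correlates r = +0.3 with a GP's underlying rate. With a normal model, the shift in the retained mean is r × φ(z_q)/(1 − q) × SD.
- φ(−0.674) = 0.318, so the shift is 0.3 × (0.318/0.75) × 7.06 = 0.90 points.
- Share of the target: 0.90/5.4 = 17%.
- With r = 0 the shift is 0. With r = −0.3 it is −0.90 points.

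A second formulation avoids the normal model. If a fraction f is dropped and their mean rate is d points below that of the retained GPs, the shift is f × d. Taking f from 10% to 30% and d from 2 to 10 points gives 0.10 × 2 = 0.2 up to 0.30 × 10 = 3.0 points, or 4% to 56% of the target. If the dropped GPs have the higher rates, the sign changes.

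**4. What baseline adjustment could remove**

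Assume a stable GP rate and 50 baseline encounters per GP. The reliability of the baseline rate is 50 × 0.02/(1 + 49 × 0.02) = 1.00/1.98 = 0.505, so the 0.90-point shift falls to 0.90 × (1 − 0.505) ≈ 0.44. With 20 encounters the reliability is 0.40/1.38 = 0.29, and the remainder is 0.90 × 0.71 ≈ 0.64.

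**5. Power**

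The loss is small. At 20 encounters per GP, two-sided, reducing only the QC arm from 100 to 80 GPs takes power from 0.833 to 0.788. The problem is bias, not precision.

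**The case against.** The rule is milder than a per-protocol analysis, because non-users who had access to QC are kept. This keeps one kind of non-user, but GPs who could not get QC to work and GPs who skipped the survey are still removed, from one arm only.

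A reader might infer that the filters must favour QC, by keeping the more engaged prescribers, and so inflate the false-positive rate of the one-tailed test. The document does not support that. Disengaged GPs with access stay in. GPs who try QC are the ones placed to meet technical problems, so that filter may remove motivated GPs and work against QC. The argument is more plausible for the survey filter, but it is still conjecture. Any false-positive rate would rest on an assumed positive correlation, removal share and number of encounters, so none is put forward here.

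Baseline data are the strongest counter-argument. Twelve months of earlier prescribing are collected and the plan speaks of adjusted data, which addresses selection on a GP's stable rate. It would reduce the bias, as shown above. The article does not state the method, and adjustment cannot be relied on to remove selection on motivation or on response to QC.

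A reader might also infer that the filters certainly remove failures from the acceptance-and-use outcome. That is only one reading. The exclusions are paired with a control rule about prescribing data, and utilisation has its own sentence, so they fit the prescribing comparison more naturally. But they are tied to the primary outcome, and use is one, so the wording is ambiguous.

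**Conclusion.** The point stands: the plan is wrong as written. Its primary prescribing comparison is defined by arm-specific, post-randomisation rules that contradict its own intention-to-treat label, and no other section resolves this. That conclusion rests on the text alone.

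The size and direction of the resulting bias cannot be determined from the document. The 0.9-point shift (17% of the 5.4-point target) depends on the assumed 25% removal and correlation of +0.3, before baseline adjustment. Other assumptions give less, more, or the opposite sign. The effect on reported use and acceptance is a possible reading that needs clarifying, not an established error.

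**What to change.** Define the primary prescribing set by one rule for both arms: every randomised, consented GP with post-randomisation prescribing data, analysed as allocated. Restricting to consented GPs is sound because allocation is disclosed only after consent. Treat GPs who have only the 6-month extraction in the same way in both arms.

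Delete the survey and technical-difficulty conditions from the primary analysis. If the present set is of interest, keep it as a labelled secondary or per-protocol analysis.

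State that use of QC is reported over all GPs allocated to it, with a GP who has no logged search counted as a non-user.

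The change needs analysis wording only and no new data. Including GPs who could not use QC may dilute the estimate slightly.

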### Data collection

The timing and content of study assessments are summarised in Table 5. Frequency and purpose of system use of QC are determined from automatically generated computer logs used to record details of each search including the search filter chosen, keywords entered, data sources accessed, user IP (Internet Protocol) address, date, time and duration of searches [see Additional file 4]. Users are asked to identify if the IP address is their home or consulting room. An online feedback facility within the QC user interface is used to record clinicians comments in context of specific searches that generate the feedback (Figure 2).

Participants in both the control and intervention group provide prescribing data in electronic format [see Additional file 5]. The data extraction process excludes all potentially identifying information such as patient name, address, gender, postcode, telephone number, Medicare number, progress notes, images (e.g. X-rays) and any data fields that could identify a patient, such as free text fields. Data for the study period (i.e. 12 months retrospective data plus 12 months of the intervention period) is electronically extracted from prescribing software using secure means without any intrusion on clinicians' work.

The prescription data extraction software and installation instructions are sent by email and also are made available online. The first data extraction (i.e. retrospective prescriptions data from the previous 12 months) is performed after installation of the extraction software at the start of the study. The second extraction is scheduled at 6 months and the final at 12 months. An uninstall program will remove all extraction software, created files and changes to profiles in clinicians' prescribing software. At the end of 12 months all participants complete a post-trial survey [see Additional file 6]. Participants attitudes to information seeking and responses to the psychometric instrument used in the pre-trial survey are repeated post-trial.

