#### Randomisation, blinding and allocation concealment

Eligible GPs are stratified by gender and randomised to the intervention or control group using a computer generated random number sequence in randomly assigned blocks (max. block size 8) and online evidence allocation ratio of 1:1. For each level of strata, a random sequence of study group assignments is generated using a computerized random-number generator [12]. Each level of strata are numbered consecutively. Each doctor receives the next consecutive number in his or her stratum.

Since QC is a behavioural intervention it is not possible to blind participants to the intervention. However investigators are blinded to group assignment. The randomisation sequence is generated and clinicians are randomly assigned to two groups by a researcher from the Evaluation team of the Centre for Health Informatics. This individual is not directly involved in the study nor its analysis.

The group assignment is revealed to clinicians online only after they consent to participate in the study following completion of the pre-trial survey. To minimise contamination of control participants who might work closely with practitioners who are part of the intervention group, only one clinician is eligible to participate in the trial from each practice. In cases where there are multiple registrations from a single practice, only the first registrant is eligible to participate. Participants in the intervention group are asked not to share their QC access details with their colleagues.

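### The primary analysis is called intention to treat, but it excludes randomised GPs on events after allocation is known, under different rules in the two arms

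*Protocol article*

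**What the plan says.** All of the inclusion rules are in the Statistical analyses section of the protocol article.

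- Control arm: "All of the control group except those who did not provide prescribing data will be included in the primary analysis".
- Intervention arm: "The subset of the intervention group analysed for primary outcome will have completed the post-trial survey and provided prescribing data".
- A further rule for the intervention arm only: "Participants in intervention group who encounter technical difficulties in using QC will be excluded from this analysis". GPs who could have used QC but did not are kept.
- The label: "Using an intention to treat analysis adjusted data will be analysed".

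Two other sections fix the timing. Under Randomisation, blinding and allocation concealment: "The group assignment is revealed to clinicians online only after they consent to participate in the study following completion of the pre-trial survey". Under Data collection, the first extract is retrospective and covers the 12 months before the trial. Then: "The second extraction is scheduled at 6 months and the final at 12 months". That section also has all participants, in both arms, complete the post-trial survey at the end of the 12 months.

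**The concern.** An intention-to-treat analysis keeps randomised participants in their assigned arm whatever happens afterwards. Here, membership of the primary set depends on three later events: supplying data, returning a survey, and having working access to QC. The first applies to both arms. The other two apply to the intervention arm only.

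The survey rule is hard to defend. The primary prescribing outcome comes from the extracts and does not need the survey. An intervention GP with complete prescribing data but no survey is left out, while a control GP in the same position is kept. Observed outcome data are thus discarded in one arm only. The technical-difficulties rule has no counterpart among controls, who have no QC access, so the GPs it removes cannot be matched by a similar group of controls.

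What is at stake is whether the two analysed groups are still comparable. If GPs who return surveys or get the system working prescribe differently from those who do not, part of the observed difference reflects selection, while the label tells readers that randomisation has been preserved.

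**Working it through.** **Step 1. The rules side by side (Statistical analyses)**

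| Requirement for the primary set | Control | Intervention |
|---|---|---|
| Prescribing data supplied | yes | yes |
| Post-trial survey completed | no | yes |
| No technical difficulties with QC | not applicable | yes |

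**Step 2. Timing.** The stated order is randomisation, consent and pre-trial survey, disclosure of the allocation, the 6-month extract, then the 12-month extract and post-trial survey. GPs who never consent leave before they know their arm, so by this sequence that loss should not depend on allocation. The 6- and 12-month extracts, the post-trial survey and any trouble with QC all come after disclosure, so loss at those points can depend on it.

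**Step 3. Form of the bias.** Let L be the share of an arm excluded and D the mean prescribing rate of excluded GPs minus that of retained GPs. The retained mean equals the full-arm mean minus L × D. The bias in intervention minus control is therefore

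L(control) × D(control) − L(intervention) × D(intervention).

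If D is the same in both arms, this is [L(control) − L(intervention)] × D.

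**Step 4. Scale.** From Sample size considerations: control rate 53%, intervention rate 58.4%, intracluster correlation 0.02.

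- Target difference: 58.4 − 53 = 5.4 points.
- Between-GP SD: √(0.02 × 0.53 × 0.47) = 0.0706, or 7.06 points.

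**Step 5. Illustrations.** The article states no loss rates and no values of D, so those below are assumed.

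- Loss of 30% in controls and 15% in the intervention arm, same D in both. With D = 0.5 SD: 0.15 × 0.5 × 7.06 = 0.53 points, or 10% of 5.4. With D = 1 SD: 0.15 × 7.06 = 1.06 points, or 20%. Swapping the arms reverses the sign only. Equal loss with equal D gives zero.
- Exclusion in one arm only, as the survey and technical rules would produce. With 10% excluded and D = 5 points, 0.10 × 5 = 0.5 points. With 20% and D = 10 points (10 / 7.06 = 1.4 SD), 0.20 × 10 = 2 points. With 30% and 10 points, 3 points.

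**Step 6. Value of a GP with only the 6-month extract.** Take the variance of a GP's rate as proportional to v(m) = [1 + (m − 1) × 0.02] / m, where m is encounters per year (assumed). The information kept is v(m) / v(m/2):

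- m = 20: 0.069 / 0.118 = 0.58
- m = 50: 0.0396 / 0.0592 = 0.67
- m = 100: 0.0298 / 0.0396 = 0.75

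Such a GP is well worth counting.

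**Step 7. The plan's own sample size.** The figure of 100 GPs per arm cannot be reproduced, because encounters per GP are not in the text shown. For 53% against 58.4% at 80% power, 1,046 independent encounters per arm are needed one-sided and 1,328 two-sided. Solving m = n × 0.98 / (100 − 0.02n) gives about 13 and 18 encounters per GP. This neither supports nor weakens the point, which concerns bias.

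**The case against.** **The article condenses a fuller plan.** Handling of incomplete extracts may be set out elsewhere, and its absence here is no fault. That stands for missing detail. It does not reach the label or the unequal rules, which the article states itself.

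**The plan keeps non-users.** Retaining GPs who had access but did not use QC is in the spirit of intention to treat, and deserves credit. One can also argue that a GP who could not get the system to work says nothing about its effect: if 10% of the arm had no benefit for that reason, a 5.4-point difference would shrink by 0.10 × 5.4 = 0.54 points. That is a reasonable secondary question, but answering it by deletion in one arm gives up the randomised comparison.

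**A reader might infer more than the text supports:**

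- *That GPs with partial extracts are dropped.* The article excludes those who did not provide prescribing data and does not define the term. A GP with baseline and 6-month extracts may well be kept.
- *That three extracts carry outcome data.* The first covers the period before the trial. Only the 6- and 12-month extracts cover the intervention, so a GP with baseline alone has no outcome to recover.
- *That controls receive nothing and will therefore drop out more.* Ethical considerations ties education points to trial completion, not to QC use, and Communication with participants lists notification of points and a summary of results without distinction by arm. Differential loss is possible, not shown, and its direction is unknown.

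**Conclusion.** The point holds. The primary set fixed in Statistical analyses contradicts its intention-to-treat label, and the exclusions differ by arm and depend on events after allocation is disclosed. This follows from the text and needs no assumption about loss.

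The size of any bias is unknown. The 0.5 to 1.1 points (10% to 20% of the target difference) and the one-arm figures of 0.5 to 3 points are scale illustrations. They rest on assumed loss rates, an assumed difference between excluded and retained GPs, and the asthma example's rates and intracluster correlation. They should not be read as an estimate, and the bias could be zero or of either sign.

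The remedy has a limit. Including all GPs with a post-randomisation extract restores those removed by the survey and technical rules. It cannot recover GPs who supplied no such extract. For them only a sensitivity analysis under stated assumptions is available.

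**What to change.** 1. Apply one rule to both arms: the primary analysis includes every randomised, consented GP with at least one post-randomisation extract (6 or 12 months), in the assigned arm, regardless of survey completion or technical difficulties with QC.
2. Define providing prescribing data accordingly, so that a GP with only the 6-month extract counts.
3. Use a GP-level model that accounts for clustering of prescriptions within GP and adjusts for the baseline extract and the gender stratum. Several models would serve. The chosen one must handle GPs observed for different lengths of time.
4. For GPs with no post-randomisation extract, add a delta or tipping-point sensitivity analysis with the shift varied separately by arm, and report the number of such GPs and their baseline rates by arm where a baseline extract exists.
5. Report the subset now described as a secondary complete-case or per-protocol analysis, and do not call it intention to treat.

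The cost is a reworded analysis section and modest extra programming. No new data collection is needed. Including GPs who could not use QC may dilute the estimated effect, which then describes being offered access rather than having working access.

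### The binomial test named for the prescribing outcomes fits neither the GP as unit of analysis nor the within-GP correlation that the sample size assumes

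*Protocol article*

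**What the plan says.** In the protocol article, Sample size considerations settles the unit: "Sampling unit is the GP and the unit of analysis is also the GP". It gives the reason for a clustering allowance, "As the prescriptions belonging to the same GP will tend to be correlated", and says that "adjustments were made for intracluster correlation factor estimated to be 0.02". The worked example is asthma. Currently "53% of GP encounters for asthma lead to the prescription of a preventer medication", and with access to the system the authors expect "at least 58.4% of GP encounters for asthma lead to the prescription of a preventer medication". With 100 GPs per arm the design is said to be sufficient ("p = 0.05, power = 0.80").

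Statistical analyses then states the comparison: "Using an intention to treat analysis adjusted data will be analysed to determine differences in prescribing patterns", together with non-pharmacological management, by a "one-tailed binomial test for proportions". It does not say what the data are adjusted for, whether the proportion is taken over encounters, prescriptions or GPs, or how clustering enters the test. The sentence just before it concerns baseline differences in prescribing, case-mix and participant profile.

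**The concern.** The sample size calculation and the named test rest on different assumptions. A binomial test takes the count of successes as a sum of independent yes/no observations, so its variance has no component for differences between GPs. The sample size section says that this component exists and puts a value on it.

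Changing the unit does not resolve the conflict. If the observation is an encounter or prescription, independence fails by the protocol's own statement. If the observation is the GP, each GP contributes a rate, and a rate is not a binary outcome. The article describes no rule that would turn a GP's rate into a yes/no result.

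Prescribing change is part of the primary outcome, and Table 1 lists eight clinical areas in which it is to be examined. If the between-GP variance is left out, the standard error is too small by the square root of the design effect in each of those comparisons. A one-tailed test then finds the expected change too often when there is none.

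**Working it through.** **Inputs from the protocol article.** 53% versus 58.4%; ICC 0.02; alpha 0.05; power 0.80; 100 GPs per arm (all from Sample size considerations); one-tailed test (Statistical analyses).

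**Assumed input.** m, the condition-specific encounters per GP. The sample size section refers to Table 4, which is not in the available text, so a range is shown.

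**Step 1: the plan's own figure.** A 10% relative increase on 53% is 0.53 × 1.10 = 58.3%, close to the stated 58.4%. Ignoring clustering, encounters per arm are

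n = [z(1−α)·√(2p̄q̄) + z(0.80)·√(p₁q₁ + p₂q₂)]² / (p₂ − p₁)²

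With p₁ = 0.53, p₂ = 0.584 and p̄ = 0.557:

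- one-sided: (1.645 × 0.7025 + 0.842 × 0.7015)² / 0.054² gives 1,046;
- two-sided (1.960 in place of 1.645): 1,328.

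GPs per arm = n × DE / m, where DE = 1 + (m − 1) × 0.02.

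- One-sided, m = 13: 1,046 × 1.24 / 13 = 99.8. At m = 12 it is 106.3, so 13 is the smallest m for which 100 GPs suffice.
- Two-sided, m = 18: 1,328 × 1.34 / 18 = 98.9. At m = 17 it is 103.1.

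The stated 100 per arm is therefore plausible if m is at least 13 (one-sided) or 18 (two-sided). It cannot be reproduced exactly without m.

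**Step 2: error of the named test on pooled, unadjusted encounters.** True one-sided error = 1 − Φ(1.645 / √DE).

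| m | DE | 1.645/√DE | True error at nominal 5% |
|---|---|---|---|
| 5 | 1.08 | 1.583 | 5.7% |
| 10 | 1.18 | 1.514 | 6.5% |
| 13 | 1.24 | 1.477 | 7.0% |
| 18 | 1.34 | 1.421 | 7.8% |
| 20 | 1.38 | 1.400 | 8.1% |
| 50 | 1.98 | 1.169 | 12.1% |
| 100 | 2.98 | 0.953 | 17.0% |

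**Step 3: simulation check.** Beta-binomial data with no true difference, 100 GPs per arm, p = 0.53, ICC 0.02 and 20,000 runs per m gave 6.6% at m = 10, 8.4% at 20, 11.7% at 50 and 16.7% at 100, in line with the formula. A t-test on GP-level proportions in the same data sets held 4.8% to 5.2%.

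**Step 4: sensitivity to the ICC.** At m = 50 the formula gives 8.9% with an ICC of 0.01 and 18.8% with 0.05. These two ICC values are assumptions; the protocol gives only 0.02.

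**The case against.** The strongest reply is that the article never says observations will be pooled as independent. It declares the GP as unit of analysis, recognises the correlation, and expresses the target as a mean prescribing rate per GP. Authors who write this may well intend a clustering allowance that a condensed article leaves out. Data can also be adjusted before a test for proportions: dividing counts by a design effect (a Rao–Scott type correction) and then applying a binomial test would control the error. Adjustment for each GP's own prescribing in the 12 retrospective months could also remove some of the between-GP variance.

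Much of this stands. Pooling is an inference, so a reader should not conclude that the trial plans to ignore clustering; the text shows two sections that do not agree. It does not follow, though, that nothing is wrong. The article commits to a particular test, and that test as named conflicts with its stated unit and correlation. The reference to adjustment follows a sentence on baseline and case-mix differences, which makes that the more natural reading, and case-mix adjustment alone does not put between-GP variance into the standard error. If a design-effect correction was meant, the article does not say so.

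It is also fair that m is unknown, and that for m of 5 to 10 the inflation is small (5.7% to 6.5%).

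**Conclusion.** The point holds as a conflict between the named test and the protocol's own assumptions. Its size is conditional on three things: that the test is applied to pooled encounters or prescriptions, that no cluster adjustment is made, and that the ICC is 0.02. On those terms the one-sided error is about 7% to 17% for an assumed m of 13 to 100. The lower end is the one tied to the protocol's figures, since m must be at least 13 for 100 GPs per arm to reach 80% power one-sided.

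Two stronger readings are not supported. A reader might infer that the type I error is well above 5% whatever the data look like, but that needs a value of m which the available text does not give. A reader might also infer that false positives become two to three times as frequent. The ratios to 5% are 1.4 at m = 13, 1.6 at 20, 2.4 at 50 and 3.4 at 100, so that description fits only the middle of the range.

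**What to change.** In Statistical analyses, replace the binomial test with one of two analyses:

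- a comparison of GP-level prescribing rates between arms, which matches the unit of analysis already declared; or
- a GEE or binomial mixed model on encounters or prescriptions with GP as the cluster.

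State the denominator of each proportion. Say what the data are adjusted for and how the adjustment enters the analysis. If a design-effect correction to the counts was intended, write it down explicitly.

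The cost is a change of wording and a standard method, with no new data or recruitment. Any intervals reported will be wider than those from pooled counts, by a factor of √DE (about 1.4 at m = 50). The sample size already allows for this, because it was inflated for the same ICC.
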